## Abstract

Stroke is a leading cause of long-term disability, resulting in motor impairments that significantly affect the quality of life. Predicting motor recovery is particularly difficult for people with severe motor impairment early after stroke. Traditional assessments are limited in terms of residual muscle activity, which is crucial for tailoring rehabilitation interventions. Incorporating surface electromyography (sEMG) assessment can provide a deeper understanding of motor recovery potential in severe motor impairment. This prospective cohort study aims to develop a TRIPOD-compliant prediction model to examine whether sEMG amplitude recorded from five upper and four lower extremity muscles within the first week of stroke could predict motor recovery at 3 months post-stroke. This prospective study will include 76 participants between the ages of 18–80 years presenting first-ever anterior or middle cerebral artery stroke resulting in a severe motor impairment within the first week of stroke onset. In addition to sEMG recording to evaluate muscle activity, participants will undergo a comprehensive clinical assessment of motor functions and activity at the 1st and 3rd months following stroke onset. Multivariate regression analyses will be used to determine associations between sEMG metrics and recovery outcomes.

## Specifications table

**Table utbl0001:** 

Subject area	Neuroscience
**More specific subject area**	Stroke
**Name of your protocol**	Predicting motor recovery using surface electromyography in people with severe motor impairment after stroke: A prospective cohort study protocol
**Reagents/tools**	• Electromyography (Delsys, Trigno wireless EMG 8-channel AD instrument, USA) • Action Research Arm Test Kit
**Experimental design**	Not applicable
**Trial registration**	CTRI/2025/06/088335
**Ethics**	Before the study commencement, all participants will provide written informed consent.
**Value of the Protocol**	• This study explores sEMG as an early biomarker of residual muscle activity, potentially enabling more accurate prediction of motor recovery in people with severe motor impairment than conventional clinical assessments alone. • By identifying patients with residual motor potential despite severe initial motor impairment, the resulting prediction model can guide individualized rehabilitation intensity and goal setting, optimizing functional outcomes. • Few studies have focused on individuals with severe motor deficits in the acute phase. This protocol generates novel evidence that could reshape prognostic practices and inform future research in this high-risk population.

## Background

Stroke is a significant contributor to death and long-term disability worldwide [1]. Poststroke motor impairment is the most prevalent cause of adult disability, which has a major impact on healthcare worldwide [[2], [3], [4]]. Such impairments limit the capacity to carry out activities of daily living (ADL) [5], with >70% of stroke survivors experiencing hemiplegia affecting the upper or lower limbs, thereby affecting their functional independence [6]. According to International Classification of Functioning, Disability and Health (ICF) [7], motor functions encompass neuromusculoskeletal and movement-related functions, including muscle strength and endurance; voluntary movement control and coordination; and movement patterns related to walking, transfers, or upper body tasks [8].

Stroke recovery, in turn, refers to the extent to which functioning at different levels (body structure/function, activity capacity, and performance or participation) has returned to a prior stroke level [9]. Recovery is a multifaceted process that possibly combines spontaneous and learning-dependent processes, including restitution (repairing the impaired neural tissues), substitution (reorganizing partially impaired neural tissues to regain lost functions), and compensation (improving the gap between a patient's impaired skills and the demands of their environment) [10]. Even though recovery trajectories differ among individuals, several studies have suggested that recovery of body functions and activities is predictable even in the first days of stroke [10,11].

The capacity to estimate motor recovery would improve health resource use, individual-tailored rehabilitation programs, and patient and therapist expectations. Nevertheless, predicting motor function recovery remains a significant challenge owing to the high degree of variability among individuals, particularly when prediction relies solely on clinical evaluation [12]. While clinical assessment can serve as a strong independent predictor, particularly for patients with mild to moderate motor impairment [13], its predictive accuracy is more limited in those with severe deficits [13]. In such cases, adding neuroimaging and neurobiology biomarkers to prognostic models may help patients with severe motor impairments [[14], [15], [16]]. Unfortunately, the high expense, technical difficulty, and restricted accessibility of these methods in standard clinical practice limit their applicability [14].

Due to the limits of clinical evaluations and the restricted availability of advanced neuroimaging technologies, alternative, affordable, and scalable approaches to enhance the prediction of motor recovery are needed, particularly in individuals with severe motor impairments after stroke. While clinical assessments are widely used, their predictive accuracy is restricted in these cases because they cannot identify subtle neuromuscular activation [17]. This limitation often results in delayed or insufficient rehabilitation strategies, a problem further compounded by the limited availability or slow clinical translation of advanced neuroimaging and neurophysiological techniques in many clinical settings. Several prognostic models have been developed to predict motor recovery after stroke, such as the Prediction Recovery Potential (PREP) and the updated version as PREP2 [12,17]. These prediction models combine early clinical assessment of Shoulder Abduction and Finger Extension score (SAFE) with neurophysiological markers such as motor evoked potentials (MEPs) obtained through transcranial magnetic stimulation (TMS) and neuroimaging measures such as diffusion-weighted Magnetic Resonance Imaging (MRI). While these approaches have demonstrated strong predictive validity, their reliance on advanced technologies limits their feasibility in routine clinical practice. This underscores the need for alternative, accessible biomarkers that can provide similar prognostic value without the cost and complexity of TMS or MRI.

In this context, surface electromyography (sEMG) may be a promising alternative. It is an objective method that offers real-time data on muscle activity in terms of timing, location, contraction intensity [[18], [19], [20]] and can also identify subtle neuromuscular signals that will not be detected during a traditional clinical examination [21]. sEMG has the benefit of being able to monitor muscle activity even in the absence of perceptible or obvious movement [22] which is especially useful for evaluating patients with severe motor impairments and could lead to earlier and more precise prognosis [23]. Although the precise neurophysiological mechanisms underlying these early sEMG signals are not fully established, existing evidence have demonstrated measurable muscle activity through sEMG during acute care in patients classified as flaccid through conventional clinical assessment [23]. This ability strongly relates to the current study's goal, which is to investigate the prognostic value of early sEMG signals in forecasting functional outcomes and motor recovery.

Despite its advantages, the application of sEMG in early stroke recovery prediction is still unexplored in clinical practice. Currently, the majority of applications focus on biofeedback or rehabilitative monitoring rather than prognostic modelling. The lack of established procedures, limited awareness among clinicians, and differences in signal interpretation may all contribute to this underutilization. Therefore, a thorough examination of the prognostic potential of sEMG is needed, especially during the acute stage of stroke. To bridge this gap, we aimed to develop a prediction model for people with severe motor impairment after stroke, employing surface electromyography to analyse whether the amplitude of muscle activity recorded from upper limb muscles such as anterior deltoid, middle deltoid, long head of biceps brachii, long head of triceps brachii and extensor carpi radialis and lower limb muscles such as tibialis anterior, medial head of gastrocnemius, rectus femoris, and biceps femoris within the first week of stroke could predict upper and lower extremity motor recovery and activity capacity of the upper extremity, postural balance, and walking at 3 months post stroke. These muscles were selected because they represent key proximal and distal muscle groups commonly involved in upper and lower extremity functions, balance and walking functions after stroke [24,25]. We hypothesized that greater sEMG amplitude recorded within the first week post-stroke, reflecting detectable voluntary muscle activity in the absence of visible movement, would be positively associated with upper and lower extremity motor recovery, upper extremity activity capacity, postural balance, and walking ability at 3 months post-stroke.

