## Participants

We will include individuals aged 18–80 years, of any sex, with a first-ever ischemic or haemorrhagic stroke affecting the middle cerebral artery (MCA) or anterior cerebral artery (ACA). Recruitment will occur within seven days of stroke onset, and individuals reporting a Shoulder Abduction and Finger Extension (SAFE) score of <5(0–4) or knee extensor strength of <3/5 on the Medical Research Council (MRC) strength grade within this period will be included. Only those who are medically stable and able to follow simple commands will be included. The exclusion criteria will be individuals with a history of bilateral clinical strokes; those admitted more than seven days after stroke onset; patients who had undergone surgical interventions such as craniotomy or craniectomy; and individuals with pre-existing neurological or musculoskeletal disorders affecting motor functions.

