### Electrode placement & task instructions

Surface EMG sensors will be positioned over the muscle belly of the affected upper and lower limb muscles in accordance with SENIAM guidelines and aligned parallel to muscle fiber orientation [29]. For sEMG recording of each muscle, participants will be instructed to perform the corresponding functional movement (eg: elbow flexion movement for the sEMG recording of the biceps brachii muscle) as depicted in Figs. 2& 3. Assistance or gentle resistance will be provided by the therapist as appropriate, depending on the participant's level of paresis. Each contraction will be recorded for a duration of 10 s, and a total of three trials will be obtained. Detailed procedures for electrode placement and recording are provided in Supplementary File 1.

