## sEMG analysis

Sensitivity analyses will be conducted where feasible to assess the robustness of the primary association between early sEMG amplitude reflecting voluntary muscle activity in the absence of visible movement and subsequent motor recovery. These secondary analyses will evaluate whether reasonable variations materially influence model performance in signal-processing assumptions and will be reported as supplementary without modifying the predefined primary analytical approach. Exploratory analysis will examine the association between early sEMG amplitude and SAFE scores recorded at baseline to provide preliminary evidence of convergent validity. Spearman correlation coefficients (ρ) with 95% confidence intervals will be reported

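### The hypothesis is about muscle activity without visible movement, but entry admits people who may move visibly, so a whole-cohort result would not by itself support it

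*Protocol article*

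**What the plan says.** Protocol article, Background: the hypothesis is that greater first-week sEMG amplitude, "reflecting detectable voluntary muscle activity in the absence of visible movement", goes with better 3-month outcomes in both limbs, in balance and in walking. The sEMG analysis section repeats the construct and calls it the "primary association between early sEMG amplitude reflecting voluntary muscle activity in the absence of visible movement and subsequent motor recovery".

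Participants: the upper-limb criterion is a "Shoulder Abduction and Finger Extension (SAFE) score of <5(0–4"). The lower-limb criterion is joined to it as an alternative: "or knee extensor strength of <3/5 on the Medical Research Council (MRC) strength grade".

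Electrode placement & task instructions: for each muscle, "participants will be instructed to perform the corresponding functional movement". The section adds: "Assistance or gentle resistance will be provided by the therapist as appropriate, depending on the participant's level of paresis". Muscles of both limbs are recorded in the cohort (Measurement time points, Table 1).

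Baseline strength has two stated uses in the analysis. In the sEMG analysis section, baseline SAFE enters an exploratory Spearman correlation with amplitude, as evidence of convergent validity. In Missing data, baseline motor severity is an auxiliary variable for the imputation model.

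**The concern.** The case for sEMG in the Background is that it picks up activity which clinical examination misses. The hypothesis turns that into a specific claim about activity that produces no movement an observer can see. To test it, the study must look at people, limbs or muscles in that state, or at least hold visible strength constant. The entry rule selects on severity, which is a different and wider condition.

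At stake is what a positive result would mean. If participants who already move visibly both give larger signals and recover better, amplitude could predict recovery in the whole cohort simply by standing in for clinical strength. The question that sets this study apart, whether sub-visible activity carries prognostic information, would remain open while the stated hypothesis appeared confirmed.

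**Working it through.** The point does not turn on the sample size, but the size limits the remedy. With the article's inputs, n = 1.96² × (1 − 0.6²) / 0.20² = 3.8416 × 0.64 / 0.04 = 61.5, stated as 61. Then 61 / 0.80 = 76.25, stated as 76. Both figures reproduce.

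**Assumptions.** The article defines neither scale. I take SAFE as the sum of two MRC grades (shoulder abduction a, finger extension b, each 0 to 5), and grade 2 or more as visible joint movement.

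**Upper-limb criterion, a + b ≤ 4.** If both grades are 0 or 1, the largest possible sum is 1 + 1 = 2. SAFE 3 or 4 therefore cannot occur without a grade of 2 or more.

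| SAFE | Grade pairs | Pairs with a grade ≥ 2 |
|---|---|---|
| 0 | 1 | 0 |
| 1 | 2 | 0 |
| 2 | 3 | 2 |
| 3 | 4 | 4 |
| 4 | 5 | 5 |
| Total | 15 | 11 |

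These are possible score pairs, not patients. The row for SAFE 2 shows that the total alone cannot identify the non-moving state: grades 1 and 1 give the same total as 2 and 0.

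**Lower-limb criterion, grade < 3.** Grades 0, 1 and 2 are admitted, and one of the three is visible movement under the assumption.

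**Stricter reading of visible.** Suppose only grade 3 or more counts. The pairs (3,0), (0,3), (3,1), (1,3), (4,0) and (0,4) still qualify, 6 of 15. The knee criterion then excludes visible knee extension, but the arm criterion still does not exclude visible movement.

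**The link between the criteria.** They are alternatives. Someone who qualifies on the arm may have any knee grade, and someone who qualifies on the knee may have any SAFE score. Both limbs can still be recorded, and the hypothesis covers both.

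**Stated analyses set against the claim.**
- The SAFE correlation measures overlap between amplitude and clinical grade. It does not remove that overlap from the association with recovery.
- Baseline severity in the imputation model helps fill in missing values. It does not adjust the association.
- The sensitivity analyses in the sEMG analysis section vary signal processing, not movement status.

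No stated analysis restricts, stratifies or adjusts by visible movement.

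**The case against.** The strongest reply is that the disputed phrase is a subordinate gloss. The Abstract and the stated aim concern amplitude in severe motor impairment, and no endpoint or performance measure depends on the phrase. That stands for the broader aim. It does not remove the conflict, because the phrase appears in both the hypothesis and the primary association.

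A reader might go further and infer that the association will be driven mainly by people who already move, citing 11 of 15 pairs (73%). The documents do not support that, for four reasons:
- No distribution of SAFE or MRC grades is given, and the count weights every pair equally. For the knee, two of the three admitted grades show no visible movement under the same assumption.
- SAFE and knee extension do not grade the movements of several recorded muscles, such as biceps brachii, triceps brachii, tibialis anterior and gastrocnemius.
- The Procedure section normalises mean RMS by maximum RMS. A within-person ratio need not rise with strength, so movers and non-movers could have similar values.
- The mention of gentle resistance does not show that a qualifying limb moves. It may apply to the limb that did not qualify.

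It may also be said that the recording details are in a supplementary file, that Model development and validation promises prespecified predictors without listing them, and that baseline strength could be among them. That is possible, so the point is limited to the analyses the article states. An unseen plan could add an adjustment, but it would not reconcile the published hypothesis with the published entry rule.

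**Conclusion.** The mismatch is real. The hypothesis and the primary association are worded for activity without visible movement, the entry rule admits participants who may move visibly, and no stated analysis tells the two apart. A positive whole-cohort association would be compatible with prognostic value of sub-visible activity and equally with amplitude standing in for clinically visible strength, so it would not by itself support the narrower claim.

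The size of the problem cannot be given, because it depends on the distribution of baseline grades and on how the normalised amplitude relates to strength. The conclusion rests on the usual meaning of SAFE and MRC grades. Under a stricter threshold for visible movement it weakens for the knee criterion but survives for the arm and through the alternative criteria. The prediction model for severe impairment is not invalidated. This should be corrected because it changes what the study can conclude and costs little.

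**What to change.** Keep the entry rule and choose one of two routes.

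1. **Reword.** In the Background and the sEMG analysis section, state the hypothesis and primary association as concerning early sEMG amplitude in severe motor impairment, and limit the conclusion to that. The cost is a narrower claim.
2. **Test the claim.** At the sEMG session, record for each muscle whether the instructed movement is visible. Prespecify one secondary analysis in limbs graded 0 to 1, together with a whole-cohort estimate adjusted for baseline SAFE and knee MRC grade. The code is needed because the SAFE total does not identify the state and the entry grades do not cover every muscle. It should be in place before recording begins. The cost is one bedside code per muscle and a subset estimate that will be imprecise, since the subset is only part of about 61 completers.

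Do not add a movement interaction for every muscle. Nine interaction terms alone would exceed the budget of about 7 parameters in Sample size estimation. If the subset proves too small to be informative, fall back on the first route.

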## Description of protocol

This is a prospective, single-center cohort study designed for the development and internal validation of a multivariable prognostic model, reported in accordance with the Transparent Reporting of a multivariable prediction model for Individual Prognosis or Diagnosis (TRIPOD) guidelines [26]. This longitudinal single-group cohort study will be conducted at the stroke unit and the neuromotor control unit of a tertiary care hospital in South Karnataka, India. Participants will be selected using a purposive sampling method. This study was approved by the Institutional Ethics Committee (IEC- 123/2025) and registered with the Clinical Trial Registry-India (CTRI/2025/06/088335).

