## Sample size estimation

The sample size was estimated using the following formula:$$n={\left(Z\alpha /2\right)}^{2}\left(1-r^{2}\right)/d^{2}$$where Zα/2 (Confidence Interval) = 95%, CI = 1.96, r (Estimated Correlation value) = 0.6, and d (Precision) = 20%.

Considering the above values, *n* = 61

Thus, with a dropout rate of 20%. *n* = 76

Hence, the final sample size of this prospective cohort study was 76 participants with stroke.

The sample size determination is guided by a widely accepted rule of thumb for prediction modelling, which recommends approximately 10 outcome events per predictor parameter [27]. Based on this principle, the available sample size is expected to support the inclusion of a small and clinically meaningful set of predictors, anticipated to be around 7 (≈7 degrees of freedom) while minimizing the risk of overfitting. Consistent with guidance by Riley et al [28] we considered a target global shrinkage factor of ≥0.90 to limit overfitting and aimed for an anticipated discrimination performance (AUC) of approximately 0.75–0.80. Furthermore, the modelling strategy will incorporate penalised regression techniques and bootstrap-based internal validation to obtain optimism-corrected estimates of discrimination and calibration, consistent with TRIPOD recommendations.

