## Procedure

All patients admitted with acute stroke to the study center during the recruitment period will be consecutively screened within the first week of stroke onset for eligibility. A screening log will be maintained to document the number of patients screened, included, excluded (with reasons), and those who decline participation. Information recorded in the screening log will inform the final participant numbers, as summarised in the study flow diagram (Fig. 1). Patients who fulfil the inclusion criteria will be requested to participate in the study. The measurements will be recorded the next day after the consent for participation. Raw sEMG signals will be collected from the paretic side at two time points—within 7 days and again at 30 days after stroke onset and processed via Lab Chart 8.1.30 software. The raw data (%Maximal Voluntary Contraction) will be normalized by the mean Root Mean Square (RMS) /max RMS X100, which will be used for analysis. Mean RMS will be computed for each 10-second trial during task execution and then averaged across trials. The following clinical assessments will be collected at the 1st and 3rd months after stroke onset: Fugl Meyer Assessment (FMA), Action Research Arm Test (ARAT), Functional Ambulation Category (FAC), 10-meter Walk Test (10MWT), Mini BEST, and Stroke Impact Scale (SIS)Version 3.0. During the hospitalization phase, all the measurements will be performed in a quiet room next to the stroke unit. During follow-up, a recording will be performed at the physiotherapy department. To minimise detection bias, assessors conducting clinical outcome assessments at the 1st and 3rd month follow-ups will be blinded to baseline sEMG measurements. Assessments will be performed by a licensed neurophysiotherapist with formal training in standardised stroke outcome measures. The investigator responsible for sEMG acquisition will be a neurophysiotherapist trained in sEMG recording, will not be involved in outcome assessments, and will remain blinded to all follow-up outcomes.

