## Internal validation and model performance

Internal validation will be performed using bootstrap resampling to obtain optimism-corrected estimates of model performance. Model calibration will be evaluated by reporting the calibration intercept and calibration slope. Discrimination of the model will be assessed using the area under the receiver operating characteristic curve (AUC). Overall model performance will be quantified using the Brier score. The primary endpoint will be analysed as a (ΔFMA) as continuous outcome. Secondary analyses will explore clinically meaningful dichotomous thresholds for recovery based on published guidelines and expert consensus. Decision-curve analysis will be used to assess the net clinical benefit of the prediction model across a range of clinically relevant thresholds. In addition, repeated cross-validation using leave-one-out cross-validation (LOOCV) will be conducted as a sensitivity analysis to evaluate the robustness of model performance estimates.

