## External validation

Following internal validation, external validation in an independent or temporally distinct cohort will be conducted in future work to further evaluate model generalizability and clinical utility.

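### The design section names purposive sampling while the Procedure describes consecutive screening; the two need reconciling, because judgement-based choice among eligible patients could alter the case mix on which the model is built.

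*Protocol article*

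**What the plan says.** Description of protocol gives the sampling rule in one sentence: "Participants will be selected using a purposive sampling method". The same section says the study is "designed for the development and internal validation of a multivariable prognostic model".

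The Procedure describes recruitment differently: "All patients admitted with acute stroke to the study center during the recruitment period will be consecutively screened within the first week of stroke onset". It continues: "Patients who fulfil the inclusion criteria will be requested to participate in the study". On record keeping it says: "A screening log will be maintained to document the number of patients screened, included, excluded (with reasons), and those who decline participation".

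On performance, Internal validation and model performance says: "Model calibration will be evaluated by reporting the calibration intercept and calibration slope". That section also plans AUC, Brier score, decision curves, bootstrap resampling and a leave-one-out sensitivity analysis. Testing outside this cohort is deferred: "external validation in an independent or temporally distinct cohort will be conducted in future work".

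The Bias section deals with measurement error, observer bias and attrition, but not with selection into the cohort. Limitations mentions only the restriction to severe impairment and to the first three months.

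**The concern.** Purposive sampling ordinarily means that the investigator uses judgement to decide whom to take. Consecutive screening followed by an invitation to those who qualify suggests taking eligible patients as they come. Both statements are current text, and a reader cannot tell which one governs enrolment.

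The difference matters because this cohort is used to build a prognostic model and to report how well it performs. Correlation, R² and AUC all depend on how varied the enrolled patients are. If patients are chosen for their apparent residual activity, those measures describe the chosen mix and not the stroke-unit population. If they are chosen for expected recovery in ways the predictors do not capture, the predicted outcomes themselves may be off for the wider population. Internal validation resamples the enrolled patients, so it would show neither problem, and no external check is planned within this study.

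**Working it through.** **The passages side by side**

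| Step | Description of protocol | Procedure |
|---|---|---|
| Who is screened | not stated | all acute stroke admissions, consecutively |
| Who is invited | chosen purposively | patients who meet the criteria; neither 'all' nor 'in sequence' is stated |
| What is recorded | not stated | screened, included, excluded with reasons, declined; no entry for eligible but not approached |

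Consecutive screening is not the same as consecutive enrolment. A site could screen every admission, choose among those eligible, and comply with the wording of both sections. The texts therefore do not exclude each other at every step. What they leave open is the step that matters, from eligible to invited.

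**The plan's own sample-size figure**

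Sample size estimation gives "r (Estimated Correlation value) = 0.6, and d (Precision) = 20" per cent, with z = 1.96.

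- n = 1.96² × (1 − 0.6²) / 0.20² = 3.8416 × 0.64 / 0.04 = 61.47, stated as 61.
- With 20% dropout: 61 / 0.8 = 76.25, stated as 76.

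These figures reproduce to within rounding, and the sampling question does not alter them.

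**Illustration of a shift in correlation**

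Assumptions, none of them from the documents:

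- the 0.6 is the predictor–outcome correlation among all eligible patients (the article does not say which pair of variables it describes);
- predictor and outcome are bivariate normal;
- selection acts on the predictor alone, with the cut-offs shown.

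If v is the ratio of predictor variance after selection to that before, and u = √v, then

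r′ = r·u / √(1 − r² + r²·u²), with r = 0.6.

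| Assumed selection | v | Calculation | r′ | r′² |
|---|---|---|---|---|
| None | 1 | – | 0.60 | 0.36 |
| Upper half | 1 − 2/π = 0.363 | 0.6 × 0.603 / √(0.64 + 0.36 × 0.363) | 0.412 | 0.17 |
| Upper two-thirds | 0.468 | 0.6 × 0.684 / √(0.64 + 0.36 × 0.468) | 0.456 | 0.21 |
| Outer thirds | 1.47 | 0.6 × 1.212 / √(0.64 + 0.36 × 1.47) | 0.673 | 0.45 |

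The shift can go either way: taking one end of the range lowers the correlation, and taking both extremes raises it.

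**What this does and does not say about calibration**

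In this set-up selection depends only on the predictor X, so the mean outcome given X is the same among selected and unselected patients. The regression intercept and slope do not change. Correlation, R² and discrimination do. For the calibration intercept to be wrong in the wider population, selection would have to depend on the outcome given the predictors, for instance on a clinical impression of likely recovery that the model does not contain. The table does not calculate that case.

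**The case against.** The strongest reply is that 'purposive' is a single label with no procedure behind it, whereas the Procedure is the operational text. The word may loosely mean selection by predefined characteristics, namely the stroke type and severity criteria under Participants, and that would fit consecutive screening. This is a plausible reading, and it limits the point. If it is the intended one, the sampling statement is simply worded wrongly and still needs changing.

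Three further arguments carry weight:

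- **Motive and means.** No section says patients are picked for cooperation, attendance or prognosis. The sEMG amplitude is not known when patients are approached, since measurement takes place the day after consent. Only clinical proxies are available then, and the eligibility criteria already restrict them. Selection as sharp as in the illustration is therefore unlikely.
- **Calibration.** A reader might take the values 0.41 to 0.67 as evidence of a miscalibrated model. They are not, because selection on the predictor leaves the regression line unchanged.
- **The log.** The number of eligible patients not approached might be recovered by subtracting included, excluded and declined from screened. That works only if such patients are not counted as excluded, and the reason they were passed over would still be missing.

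The possibility that the full protocol gives more detail does not dispose of the matter. The article is not silent on sampling; it states a method that its own Procedure does not bear out.

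**Conclusion.** The inconsistency is real and worth correcting before or during recruitment, because choices that were not logged cannot be reconstructed afterwards. Read literally, the sampling statement permits judgement-based choice among eligible patients. Its foreseeable effect is a changed case mix, and with it changed correlation, R² and AUC. An effect on calibration is conditional: it needs selection on expected recovery or on other factors outside the model. Validation within the same cohort would reveal neither.

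The size is unknown. The range 0.41 to 0.67 around 0.6 rests wholly on the assumptions listed above and shows only that correlation could move in either direction.

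Two stronger inferences are not supported. One is that the cohort will be hand-picked: the text permits this but does not announce it. The other is that the two sections cannot both be followed: a site could screen consecutively and then choose, and the Procedure does not say that every eligible patient is invited.

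**What to change.** 1. Under Description of protocol, replace purposive sampling with consecutive enrolment of all eligible, consenting patients until 76 are enrolled.
2. In the Procedure, state that all eligible patients are invited.
3. Add to the planned screening log the category 'eligible, not approached (reason)'.

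If judgement-based selection is in fact intended, the article should give its criteria and acknowledge the resulting limit on the performance estimates and on generalisability.

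The cost is small: two sentences and one more log column, with no additional patients or measurements and no change to the sample size. The real concession is that the investigator gives up discretion over whom to approach.
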